**I. Purpose, Background and Rationale**

**A. Aim and Hypotheses**

1. Frailty is a biological syndrome of decreased reserve and resistance to stressors arising from cumulative degradation across multiple physiologic systems. Frailty is very common in individuals living with multiple sclerosis (MS), regardless of age and level of disability. People with MS (pwMS) have up to a 15-fold higher risk of being frail compared to age-matched individuals living without MS. Frailty within MS is strongly associated with adverse clinical outcomes such as falls and negatively impacts the quality of life. Consequently, there is a critical need to identify and evaluate strategies for counteracting frailty in pwMS. People with MS become frail at a younger age compared to individuals without MS. This early onset of frailty may be an optimal window of opportunity for implementing exercise interventions aiming to reduce frailty. Reducing frailty would have a significant impact on improving the health of pwMS. To date, however, it is not known whether exercise interventions can reduce frailty in MS. The purpose of this project will be to explore the feasibility and preliminary efficacy of a multimodal exercise training program to reduce frailty in pwMS.
2. The proposed project has two research aims and one exploratory aim:

**Aim 1: To determine the feasibility of a multimodal exercise training in pwMS.**

We hypothesize that at least 80% of participants will complete the multimodal exercise training and that no serious adverse events will be recorded during the training sessions. In addition to feasibility, we will also generate the effect sizes from the intervention, which will inform the development of a fully powered randomized controlled trial (RCT).

**Aim 2: To explore the effects of the multimodal exercise training on frailty in pwMS.**

We hypothesize that participants in the multimodal exercise group will have greater reduction in frailty index than participants in the control group. Moreover, we expect that participants randomized to multimodal exercise will also exhibit a clinically meaningful change in the frailty index (i.e.,  $>0.03$ ).

**Exploratory aim: To compare pain levels in pwMS with and without frailty, as well as to explore changes in pain before and after the exercise training.**

We hypothesize that frail pwMS will have higher pain levels compared to the non-frail, and that participants randomized to the multimodal exercise training program will have a greater reduction in pain compared to participants randomized to the control group.

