### **C. Rationale**

1. There is considerable evidence that physiological function in pwMS can be improved with targeted exercise interventions. The general benefit of exercise in pwMS, highlights the possibility that a well-designed program will reduce frailty in this population. Our recently completed RCT consisting of a motor-cognitive rehabilitation intervention was successful in reducing hallmarks of frailty in pwMS. The promise shown by our program in enhancing several key moderators of frailty, seems to open the possibility that adding elements targeting frailty such as an evidence-based resistance training component will have a greater effect on reducing frailty in pwMS.
2. The main limitation of the current body of knowledge is the lack of evidence regarding the dynamic nature (i.e., modifiability) of frailty in MS. Additionally, it is not clear whether well-designed exercise-based interventions can reduce frailty in pwMS, and whether measures of frailty, such as the frailty index, are reliable (and therefore appropriate to evaluate the effects of interventions) in pwMS. Moreover, interventions in older adults designed to target frailty have had numerous methodological limitations, namely limited assessment of frailty prior to and post-intervention and lack of control groups. The current project is designed to overcome these limitations and set the foundation for interventions to reduce frailty in MS.
3. This project aims to improve the treatment of MS. This project will help determine if well-designed exercise-based interventions can reduce frailty in pwMS, which could in turn improve the overall quality of life in pwMS.

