**Aim 2: Primary Frailty Outcomes:** The primary frailty outcome of this investigation will be the frailty index. This parameter was selected based on its significant potential to quantify fine-grained changes in frailty, compared to the Fried phenotype, and on our preliminary data on frailty in MS. Notably, a recent study in hospitalized older adults has identified a change in frailty index score  $> 0.03$  as a minimum clinically important difference (MCID) in frailty status.

**Other measures:** In addition to the frailty outcomes, we will also collect sociodemographic (i.e., age, gender, body mass index, marital and occupational status) and relevant clinical measures (i.e., number of prescribed medications, disease duration, MS type) at baseline.

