### **C. Sample size, statistical methods, and power calculation**

1. Descriptive statistics (frequency/percent and mean/SD) will be mainly used to summarize participants' characteristics and intervention outcomes. The means and 95% CIs for pre-post changes in the primary (i.e., frailty index) outcome will be estimated. No imputation will be considered for missing data. The Wilcoxon rank sum test will be used for comparing the pre-post changes in frailty index between the two groups. The intervention will be considered feasible if the retention rate and the proportion of completed sessions are more than 80%. Pre-generated randomization codes will be prepared by the biostatistician ([name]). The randomization ratio will be 1:1.
2. [name], who will be the assessor for the study assessments, will be blinded to which group the participants have been allocated to. Participants will be aware of which group they are in. The study coordinator and [name] will have access to the code to the blind. The code will not need to be broken unless there are unforeseen circumstances in which [name] needs to know which group a particular participant was assigned to. Following the baseline assessment (visit 2), participants will be randomized to one of the two groups based on pre-generated randomization codes prepared by the biostatistician, [name]. In accordance with the CONSORT guidelines, sequence generation, allocation concealment and group allocation will be blinded and separate processes.
3. For this pilot study, we plan to enroll a convenience sample of 60 ambulatory people (30 per group) with Multiple Sclerosis living with frailty that meet inclusion/exclusion criteria. These subjects will provide feasibility data and preliminary efficacy data for designing a future study if the findings are promising. We expect a 15% dropout rate, and at that at least 24 subjects per group will complete the study.

**D. Subject Criteria (See Vulnerable Populations appendix, if applicable):** We will enroll 60 ambulatory pwMS living with frailty. During Visit 1, we will screen subjects for frailty based on established cut-offs according to the Fried phenotype. This screening tool was chosen to ensure a time- and cost-effective identification of pwMS who are frail.

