**V. Data Analysis and Reporting**

**A. Statistical and Data Analysis:** Descriptive statistics (frequency/percent and mean/SD) will be mainly used to summarize participants' characteristics and intervention outcomes. The means and 95% CIs for pre-post changes in the primary (i.e., frailty index) outcome will be estimated. No imputation will be considered for missing data. The Wilcoxon rank sum test will be used for comparing the pre-post changes in frailty index between the two groups.

- B. Outcome:** The intervention will be considered feasible if the retention rate and the proportion of completed sessions are more than 80%. We expect that at least 80% of participants will complete the multimodal exercise training and that no serious adverse events will be recorded during the training sessions. We expect that participants in the experimental group will have greater reduction in frailty index than participants in the control group. Finally, we expect that participants randomized to multimodal exercise will also exhibit a clinically meaningful change in the frailty index.
- C. Study results to participants:** A short, written letter of the study results will be sent to participants once the study has concluded.
- D. Publication Plan:** Findings from this study will be presented at scientific conferences and published in research journals.

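### The 0.03 benchmark for a clinically meaningful change is applied to the exercise arm's own pre-post change, so change shared with the waitlist can meet it without any treatment effect

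*Protocol*

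**What the plan says.** Section I.A, Aim 2, makes two statements. The first compares the arms and has a direction but no size: "We hypothesize that participants in the multimodal exercise group will have greater reduction in frailty index" than the control group. The second has a size but no comparator: "we expect that participants randomized to multimodal exercise will also exhibit a clinically meaningful change in the frailty index", with more than 0.03 given as the meaning. Section V.B repeats the second statement as an expected outcome: "Finally, we expect that participants randomized to multimodal exercise will also exhibit a clinically meaningful change in the frailty index".

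The source of the threshold is in section II.B: "a recent study in hospitalized older adults has identified a change in frailty index score" above 0.03 as the minimum clinically important difference.

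For analysis, sections II.C and V.A plan two things. One is estimation: "The means and 95% CIs for pre-post changes in the primary (i.e., frailty index) outcome will be estimated". The other is a between-arm test: "The Wilcoxon rank sum test will be used for comparing the pre-post changes in frailty index between the two groups". Neither is linked to 0.03. Nowhere is 0.03 applied to the difference between arms, and the protocol does not say whether it refers to the arm mean or to each participant.

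**The concern.** The pre-post change in the exercise arm is the treatment effect plus whatever would have happened over the same six weeks anyway. The waitlist exists to remove that second part. The between-arm hypothesis uses it; the statement about clinical importance does not. The rationale in section I.C faults earlier frailty trials, "namely limited assessment of frailty prior to and post-intervention and lack of control groups", and says this project is designed to overcome those limitations.

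The protocol itself makes some shared change plausible. Table 1 counts 12 of the 70 index items under cognition and physical performance, mostly tests repeated after about six weeks. People can enter once 30 days have passed since a relapse, so recovery may still be under way. Section I.B says that the test-retest reliability of the index in MS still needs study.

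At stake is how the pilot is reported. A mean fall above 0.03 with exercise could be called clinically meaningful although the waitlist fell as much. If both arms worsened, a real benefit could fail the same benchmark.

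**Working it through.** **Inputs from the protocol.** 30 per group, 15% dropout, at least 24 completers per group (II.C); threshold 0.03 (I.A, II.B); 70 items (II.E, Table 1).

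**The plan's own figure.** 30 × (1 − 0.15) = 25.5, consistent with at least 24, which is 80% of 30. I use n = 24. On the index, 0.03 × 70 = 2.1 items.

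**Assumptions not in the protocol.** SD of individual change 0.05, 0.06 or 0.08; shared improvement d from 0 to 0.03; normally distributed changes; true treatment effect zero; two-sided alpha 0.05 for the rank test.

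**Statement as written, read on the arm mean.** P(exercise-arm mean reduction > 0.03) = 1 − Φ((0.03 − d) / (SD/√24)). For example, at SD 0.06 and d = 0.02 the standard error is 0.06/√24 = 0.0122, so z = 0.01/0.0122 = 0.82 and P = 0.207.

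**Same threshold on the between-arm difference.** P = 1 − Φ(0.03 / (SD × √(2/24))). The shared change cancels.

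| SD | d = 0 | d = 0.02 | d = 0.03 | Between-arm, any d |
|---|---|---|---|---|
| 0.05 | 0.002 | 0.164 | 0.50 | 0.019 |
| 0.06 | 0.007 | 0.207 | 0.50 | 0.042 |
| 0.08 | 0.033 | 0.270 | 0.50 | 0.097 |

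The single-arm result depends strongly on d, which the trial cannot know without the waitlist. The between-arm result does not. With no shared change, however, the between-arm point estimate passes 0.03 by chance more often than the single-arm one (0.042 against 0.007 at SD 0.06), because it carries the noise of two arms. It therefore has to be read with its confidence interval.

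**Read per participant.** With no effect and no shared change, the proportion with a reduction above 0.03 is 1 − Φ(0.03/SD): 27% at SD 0.05 and 35% at SD 0.08, in either arm. An exercise-arm proportion means little without the waitlist proportion beside it.

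**Both Aim 2 statements together.** In 10,000 simulated trials per scenario with no effect (SD 0.04 to 0.10, shared improvement 0 to 0.04), a reduction above 0.03 in the exercise arm combined with a Wilcoxon p below 0.05 favouring exercise occurred with probability of about 0.025 or less.

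**Could the two statements diverge in practice?** At SD 0.06, a true between-arm difference of 0.03 has z = 0.03/0.0173 = 1.73, and approximate power is Φ(1.73 − 1.96) = 0.41. An inconclusive rank test beside an exercise-arm fall above 0.03 is a realistic result.

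**The case against.** The strongest defence is that this is an expectation, not a criterion. It is added to a directional between-arm hypothesis that has its own test, and the protocol's only formal decision rule concerns feasibility (retention and session completion above 80%). A reader might infer that drift alone could carry Aim 2, or that 0.03 decides whether a later trial is designed. The documents support neither. The joint probability of about 2.5% answers the first; on the second, the protocol speaks only of promising findings and of effect sizes. What remains is that the second statement is not made conditional on the first. Section I.B also reports clinical and statistical significance as two separate verdicts on an earlier intervention.

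A reader might also infer from the unsigned word for change that a worsening above 0.03 would count. That is strained: the stated purpose is to reduce frailty, and the preceding sentence speaks of reduction. It is a wording gap and no more.

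Nor does the trial discard its control group. The planned means and confidence intervals are not limited to the exercise arm, so the waitlist change should be available to readers.

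Regression to the mean is a tempting explanation because everyone is selected as frail on the Fried criteria. But that selection is at screening and the index baseline is at Visit 2, so much of it should occur before baseline. Repeat testing affects mainly 12 of the 70 items, while 28 are comorbidity or biomarker items. A shared improvement of 0.03 is therefore possible but not established; with none, the benchmark is rarely met by chance.

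Finally, section II.B presents 0.03 as a threshold for change. Requiring the between-arm mean difference to exceed it would be stricter than that source supports. This stands, and it shapes the fix.

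**Conclusion.** The point holds in a limited form. Both places that speak of clinical meaningfulness refer only to the exercise arm's own change, and nothing ties 0.03 to the comparison with the waitlist. With no treatment effect, the chance of meeting the benchmark on the arm mean runs from at most 3% to one half as shared improvement goes from zero to 0.03. These figures rest on an assumed SD of change of 0.05 to 0.08, assumed shared change and 24 completers; the protocol supplies only the last. The controlled Wilcoxon comparison is unaffected, and Aim 2 taken as a whole is protected. The weakness is confined to a statement about clinical importance that could be reported by itself.

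**What to change.** Reword one sentence in Aim 2 and one in V.B. In both:

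- say reduction instead of change;
- report the between-arm difference in mean reduction with its 95% CI, and read the estimate and interval against 0.03 without making 0.03 a hurdle that the difference must clear;
- report the proportion with a reduction above 0.03 in each arm, and the difference in proportions with its 95% CI;
- keep the exercise-arm pre-post mean and interval as description only.

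No new data, visits or participants are needed. The price is precision. At SD 0.06 with 24 per arm, the 95% half-width is about 1.96 × 0.0122 = 0.024 for the exercise arm alone and 1.96 × 0.0173 = 0.034 for the between-arm difference. A claim of clinical meaningfulness becomes harder to support.

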## **B. Background and Significance**

1. **Study Significance:** This proposed investigation is designed to examine the feasibility of an exercise-based intervention to reduce frailty in people living with MS. The proposed research will be the first to establish the feasibility of targeting frailty in pwMS and will begin to examine the dynamic nature of frailty in MS. This project will also yield the effect sizes necessary to power a large scale RCT to reduce frailty in pwMS. These advances will pave the way for planned prospective studies toward effective targets for diagnostics, and rehabilitation of frailty in MS.
2. MS is a chronic, immune-mediated neurodegenerative disease that affects ~1 million individuals in the United States. It is characterized by demyelination and neuronal loss. MS is one of the most common causes of non-traumatic disability among adults of 20 – 40 years globally and is second only to heart failure in direct all-cause medical costs for chronic conditions. Early in the disease process there are acute episodes of neurological deficits (i.e., relapses) resulting from acute inflammatory demyelination. The location of the demyelinating lesions determines physiological system(s) affected and symptom presentation. MS is characterized by a progressive accumulation of disability, which typically manifests through walking impairment, muscle weakness, fatigue, psychological problems, and cognitive impairment. There is a critical need to identify new approaches to promote quality of life in the MS community.

Frailty is a serious public health challenge that is poised to overwhelm global health care systems. Frailty is a biological syndrome of decreased reserve and resistance to stressors arising from cumulative declines across multiple physiologic systems. It is associated with reduced quality of life, falls, health care utilizations and early mortality. The elevated risk of adverse outcomes can occur regardless of the presence of comorbidities in frail individuals. Frailty is frequently characterized by reductions in muscle strength, reduced physical activity, fatigue, reduced gait speed and unintentional weight loss (factors which are common in MS). Frailty is more than simply the accumulation of comorbidities and represents a dynamic condition that can range from non-frail ("fit") to severely frail. Building upon the dynamic nature of frailty, there has been a call to systematically investigate intervention strategies to reduce frailty.

Although it is traditionally seen as an age-related phenomenon, frailty can occur throughout the lifespan, especially in individuals with chronic conditions, such as MS. Given that MS impacts multiple physiological systems and is characterized by muscle weakness, gait impairment, fatigue and inactivity, it is not surprising that pwMS are frequently frail. They have a 15-fold higher risk of being frail compared to age-matched individuals without MS. Up to two thirds of ambulatory pwMS meet objective diagnostic criteria for frailty, and this proportion is higher in individuals with more advanced disability. The early onset of frailty in pwMS suggests that the etiology of this syndrome in MS differs from age-related frailty. Particularly, several key pathophysiological aspects of MS, such as chronic inflammation and neurodegeneration, are likely to shape the

manifestation of frailty in people with MS. Due to the unique features of frailty in MS, it is unclear whether frailty can be reduced in MS.

3. Literature Review: Several strategies to counteract frailty have been studied in older adults. Most clinical trials have been conducted in community-dwelling older adults, wherein exercise interventions represented the main strategy, and physical function (e.g. gait and strength) measures were the main outcomes. Overall, the investigations have reported reduced markers of frailty following exercise-based interventions. Particularly, multicomponent exercise programs involving resistance training, gait and balance training represent the best strategy to improve hallmarks of frailty in frail individuals.

There is considerable evidence that physiological function in pwMS can be improved with targeted exercise interventions. Progressive resistance training has a significant effect on muscle strength and walking performance in pwMS. Exercise has also been shown to have a beneficial effect on fatigue in persons with MS. The general benefit of exercise in pwMS, highlights the possibility that a well-designed program will reduce frailty in this population. Recently we completed an 8-week RCT focusing on a multicomponent exercise program involving virtual reality treadmill training (i.e., simultaneous training of gait, balance, and cognition) in over 100 pwMS and found an improvement in multiple frailty-related measures, such as gait speed, cognition, and depression following the intervention. Nevertheless, in a preliminary secondary analysis, this intervention did not result in a clinically meaningful, nor statistically significant reduction of frailty in a small subset ( $n=20$ ) of the studied sample ( $F=1.48$ ,  $p=0.244$ ,  $\eta_p^2=0.095$ ). The limited effect on frailty is not surprising given that the intervention was not specifically designed to target frailty, nor was it an inclusion criterion. However, the promise shown by our program in enhancing several key moderators of frailty, seems to open the possibility that adding elements targeting frailty such as an evidence-based resistance training component will have a greater effect on reducing frailty in pwMS.

Many approaches and scales to evaluate frailty exist. The two main conceptualizations of frailty are *physical frailty*, as operationalized through the Fried phenotype, and the deficit accumulation model (frailty index approach). The Fried phenotype is the most commonly utilized measure of frailty and defines five core components of frailty: slowness, weakness, inactivity, exhaustion, and shrinkage. Individuals who meet at least three of these components are defined as frail. The strengths of this operationalization of frailty are its cost- and time-effectiveness, as well as its large evidence base in terms of predicting negative health outcomes in various clinical populations. On the other hand, the *deficit accumulation model quantifies frailty on a continuum*, based on the presence or absence of health-related deficits. From an operational standpoint, this model utilizes a relatively high number of health-related deficit items (at least 30 are recommended) as the basis to calculate a frailty index. Importantly, one of the main advantages of the frailty index is that its operationalization is easily adaptable to many pre-existing health datasets, which is a desirable feature in terms of clinical implementation. In addition, the health-related deficits used to calculate the index encompass various domains of function (e.g., physical, cognitive, psychosocial function, etc.), making the frailty index a *more comprehensive conceptualization of frailty*. Another strength of the frailty index

approach is that it may be more suitable than the Fried phenotype to capture the dynamic nature of frailty, namely its modifiability in response to interventions. Conversely, one of the challenges of the frailty index is that it often requires effort to identify a suitable number of health-related deficits without violating its guiding principles (described in Approach). Owing to the several physiological systems affected by MS, we recently postulated that using a comprehensive view of frailty, such as the frailty index approach, may be required to capture the complexity of frailty in pwMS, as well as to evaluate the fine-grained changes in frailty over time and in response to interventions. However, more research is required to evaluate the psychometric properties (e.g., test-retest reliability) of the frailty index in pwMS.

